**FIGURE 3 F3:**
[figure not shown]
Standard protocol items: recommendations for intervention trials (SPIRIT) schedule of enrollment, interventions, and assessment. TECAS, transcutaneous electrical cranial-auricular acupoint stimulation; HAM-D, 17-item hamilton depression rating scale; HADRS, montgomery–åsberg depression rating scale; HAM-A, hamilton anxiety rating scale; PSQI, Pittsburgh sleep quality index; SF-36, short form 36 health survey.

#### Safety Assessment

All associated research staff will be trained in the recognition of and response to AE, serious adverse event (SAE), and suspected unexpected serious adverse reaction (SUSAR) according to the standard operating procedure approved by the Institutional Review Board of The University of Hong Kong/Hospital Authority Hong Kong West Cluster. All possible events will be independently evaluated by staff who do not assess treatment outcomes. The study team will follow up with participants during the whole study period and record all adverse events on a regular basis (baseline, 2, 4, 8, and 12 weeks). In general, TECAS treatment is relatively safe, but side effects such as mild dizziness, headache and local skin irritation from electrode placement are possible and will be of special concern. SAE for treatment discontinuation will be recorded including the occurrence time, severity, duration, measurement, management, and its outcome when such events occurred, and will be immediately reported to the principal investigator ([name]) simultaneously. A safety report will be reviewed by the reviewers in the Expedited Panel through an expedited review process as stipulated. If the reviewers deem a safety report has any significant implication on the protection of patients’ safety, the report will be channeled for full review.

### Data Management

Data entry will be checked using a 5% double-entry procedure. Paper copies of measures are stored in locked filling cabinets. Anonymized measures data will be stored electronically on the National Population Health Data Center/Population Health Data Archive approved by re3data and FAIRsharing with password-protected secure, only principal investigator ([name]) having access.

### Statistical Analysis

The proportion of participants with a reduction ≥50% in MADRS from baseline was 83.3% in the TECAS group and was 80.0% in the escitalopram group in our pilot study (unpublished data). Calculated by PROC POWER in SAS, in total, 470 participants will be needed to provide 90% power to detect a difference of −10% (the non-inferior margin) between groups in the proportion of participants with ≥50% in MADRS after 8 weeks of treatment at a 1-sided significance level of 5%, assuming a 20% loss to follow-up rate. The primary outcome will be evaluated based on the per-protocol (PP) population, defined as all randomized populations without major protocol violations. The primary outcome will be assessed using a 1-tailed test at a significance level of 0.025, while secondary outcomes using a 2-tailed test at a significant level of 0.05. For the proportion of participants with a reduction ≥50% in MADRS from baseline, the Cochran-Mantel-Haenszel test, stratified by site, will be used to test a hierarchical comparison between two groups. For the change from baseline in MADRS, the longitudinal data will be analyzed by fitting linear mixed-effects models using the baseline value as a covariate and treatment, visit, and treatment-by-visit interaction as fixed effects. The same approach will be used for the other continuous variables with longitudinal data, including HAMD-17, HAMA, PSQI, and SF-36. Missing data for the primary outcome will be imputed using the multiple imputation method under the missing at random assumption. For secondary outcomes, no imputation will be performed. To assess the robustness of the primary analyses, a sensitivity analysis will be performed without multiple imputation. All statistical analyses will be performed using SAS software, version 9.4 (SAS Institute).

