**Methods/Design:**

This is a multi-center, non-inferiority, randomized controlled trial that will involve 470 patients with mild to moderate depression. Patients will be randomly assigned to either the TECAS group or the escitalopram group in a 1:1 ratio. The TEAS group will receive two sessions of treatments per day for 8 consecutive weeks, and the escitalopram group will receive 8 weeks of oral escitalopram tablets prescribed by clinical psychiatrists as appropriate for their condition. The primary outcome is the clinical response as determined by Montgomery-Åsberg Depression Rating Scale (MADRS) scores at week 8, with −10% as the non-inferior margin. The secondary outcomes include the response rate determined by 17-item Hamilton Depression Rating Scale (HAMD-17), remission rate, changes from baseline in the scores on the MADRS, the HAMD-17, the Hamilton Anxiety Rating Scale (HAMA), the Pittsburgh Sleep Quality Index (PSQI), and the Short Form 36 Health Survey (SF-36).

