### Randomization

Patients will be randomly allocated (1:1) to groups receiving either escitalopram or TECAS. Stratified blocked randomization codes will be generated by PROC PLAN using SAS software, which will be stratified by the study site. The research assistants will use the randomization codes to produce opaque, sealed envelopes. Each envelope will be labeled with a participant-specific randomization identification number and contain a treatment allocation number. After the collection of patients’ basic information, participants will be assigned a randomization identification number by study staff. By using a central randomization system composed of free telephone, short message, and E-mail, the randomization identification number and treatment allocation will be accessed after participants received their baseline clinical evaluation. Participants, clinical psychiatrists, and treatment technicians will be aware of the treatment condition. The staff assessing treatment outcomes will be blinded to treatment condition because they will be segregated in a different clinic area. The participants’ treatment allocation will be required not to be discussed with these staff or other participants.

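### The sample-size sentence states a one-sided 5% level, but 470 fits the one-sided 0.025 at which the primary outcome is tested

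*Protocol article*

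**What the plan says.** All the relevant statements concern the week-8 MADRS response comparison, and nearly all are in the Statistical Analysis section of the protocol article.

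- Sample size and power: "470 participants will be needed to provide 90% power to detect a difference of −10% (the non-inferior margin".
- Level used for sizing: "at a 1-sided significance level of 5%, assuming a 20% loss to follow-up rate".
- Level used for testing, two sentences later: "The primary outcome will be assessed using a 1-tailed test at a significance level of 0.025".
- Assumed response: "was 83.3% in the TECAS group and was 80.0% in the escitalopram group in our pilot study (unpublished data".
- Software: "Calculated by PROC POWER in SAS, in total, 470 participants will be needed". The test option is not given.

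The abstract repeats the margin ("with −10% as the non-inferior margin"), and the Randomization section gives 1:1 allocation. Nothing in the article explains why the sizing level and the testing level differ.

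**The concern.** Two levels, both labelled one-sided, are attached to the same primary comparison. A sample-size statement should let a reader recover the number from its inputs, and the level in it should be the one at which the hypothesis is tested. Here the two differ by a factor of two, so at least one part of the statement (level, power or number) does not match the calculation that was run.

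What is at stake is the justification for 470. Taken literally, the sentence describes a trial about 100 participants larger than its inputs require. A reader also cannot tell whether the claimed 90% power applies to the test that will be performed.

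**Working it through.** **Inputs, as printed.** TECAS response pT = 0.833; escitalopram response pC = 0.800; margin 0.10; power 90%; 1:1 allocation; loss 20%; total 470. That is 235 per arm, or 235 × 0.8 = 188 per arm after loss.

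**Common quantities.** Distance from the margin: 0.833 − 0.800 + 0.10 = 0.133. Unpooled variance sum: 0.833 × 0.167 + 0.80 × 0.20 = 0.2991.

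**Unpooled formula.** n per arm = (z_alpha + z_0.90)² × 0.2991 / 0.133²; total = 2n / 0.8.

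- One-sided 0.05 (the level in the sample-size sentence): (1.645 + 1.282)² = 8.564; n = 144.8, so 145; total 290 / 0.8 = 362.5, about 363.
- One-sided 0.025 (the level in the analysis sentence): (1.960 + 1.282)² = 10.507; n = 177.7, so 178; total 356 / 0.8 = 445.

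**Farrington-Manning.** Here the null variance uses response rates restricted to differ by the margin, 0.754 and 0.854, with variance sum 0.3108: n = [(z_alpha √0.3108 + z_0.90 √0.2991) / 0.133]².

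- One-sided 0.05: n = 148.0; 148 per arm; 148 / 0.8 = 185 per arm, total 370.
- One-sided 0.025: n = 181.8, so 182; 182 / 0.8 = 227.5, so 228 per arm, total 456.

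**Other options tried**, because the article does not name the test. Totals are after dividing by 0.8 and rounding up to whole, equal arms, which is why the unpooled 363 and 445 appear as 364 and 446.

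| Method | One-sided 0.05 | One-sided 0.025 |
|---|---|---|
| Unpooled | 364 | 446 |
| Farrington-Manning | 370 | 456 |
| Continuity-corrected | 400 | 484 |
| Null variance at 80% / 70% | 410 | 508 |

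At 0.05 every total lies 13% to 23% below 470. At 0.025 the totals fall on both sides of 470; Farrington-Manning and the continuity-corrected size are within 3% of it. Inflating by 1.2 instead of dividing by 0.8 lowers every total, so it moves the 0.05 column further from 470.

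**Power with 188 evaluable per arm.** Unpooled standard error: √(0.2991 / 188) = 0.0399, and 0.133 / 0.0399 = 3.334.

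- One-sided 0.05: Φ(3.334 − 1.645) = 95.4% (Farrington-Manning 95.1%).
- One-sided 0.025: Φ(3.334 − 1.960) = 91.5% (Farrington-Manning 90.9%).

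The stated 90% is therefore about 5 points away from the result at the stated level, and within 2 points of the result at 0.025.

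**The case against.** The strongest reply is that the decision rule is not in doubt. One sentence says how the primary outcome will be tested, at 0.025, and contrasts this with a two-tailed 0.05 for the secondary outcomes. The 5% appears only as an input to the sample size. This stands. A reader might infer that the article leaves two rival decision rules open, so that a 90% interval could be chosen after the data are seen and the type I error doubled. That would require setting aside the explicit analysis sentence, and the document does not support it.

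A second reply is that the mismatch does no practical harm: the trial has about 91% power at the stricter level actually used. This also stands under the printed rates. A reader who infers that the trial is underpowered because of the mismatch would be wrong.

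A third reply concerns how firmly 0.025 can be identified as the level behind 470. The unpooled formula returns exactly 470 at 0.025 only if 83% replaces the printed 83.3% (188 per arm; 376 / 0.8 = 470), and the article does not print 83%. With the printed rates the match is close but not exact, and it depends on an unstated test option; one option tried, with null variance at 80% / 70%, gives 508 and 87.6% power at 188 per arm. Other inputs can also come near 470: equal rates of 80%, a one-sided 5% level, 80% power and inflation by 1.2 give 476, but these contradict the stated rates and power. So it is a strong inference, not a documented fact, that 5% is the misstated figure, perhaps a two-sided 5% labelled one-sided. What does not depend on that inference is that the printed 5%, 90% and 470 do not fit together under any option tried.

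**Conclusion.** The sample-size sentence is wrong as written. At its stated level, the printed inputs need about 363 to 370 participants by the unpooled and Farrington-Manning formulas and at most 410 by any option tried, and 470 gives about 95% power instead of 90%. At one-sided 0.025 the need by the same two formulas is about 445 to 456 and the power about 91%, so 470 belongs with the level in the analysis sentence.

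The conclusion rests on the printed 83.3% and 80.0%, a 10-point margin, 20% loss and normal-approximation formulas. It corrects a stated planning figure; the 0.025 analysis threshold and the sample size are unaffected.

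**What to change.** In the sample-size sentence of the Statistical Analysis section, replace the one-sided 5% level with a one-sided 2.5% level, so that it matches the analysis sentence. In interval terms, the lower limit of the two-sided 95% confidence interval for the difference (TECAS minus escitalopram) is compared with −10%. Keep 470. Add the response rates and the test option actually entered in PROC POWER, taken from the stored program and not back-calculated, so that the number can be reproduced. If that program shows a level of 0.05, the rates, power or loss allowance that produced 470 must differ from those printed and should be stated instead.

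The cost is a text correction and a look at the stored program. Sample size, recruitment and the primary test do not change.

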### Participants

Four hundred and seventy patients with mild-to-moderate depression will be recruited *via* hospitals, posters, and web advertisements. Participants will be recruited after referral to specialty psychiatrists at five hospitals. We will recruit adults aged 18–70 years who have a confirmed diagnosis based on the International Classification of Diseases 10th Edition (ICD-10, F32) of mild-to-moderate depression. A patient will be eligible if their current episode shows a Montgomery-Åsberg Depression Rating Scale (MADRS) score of at least 12 and less than 30; and all responses to the Suicide Severity Scale (C-SSRS) were “no” or scored <3 points. The exclusion criteria including the patients with severe diseases of heart, brain, liver, kidney or hematopoietic system, with acute diseases, infectious diseases or malignant tumors; with any history of psychosis or mania; with cognitive disorders or personality disorders; with serious suicidal ideation or behaviors; the patients who unable to stop taking relevant drugs according to the treatment requirements, or pregnant. Professional psychiatrists will be responsible for the assessment of the mentioned disorders in exclusion criteria based on the appropriate clinical diagnostic criteria in China. Participants were prohibited to use any other drug or non-pharmacological therapy, including phytomedicine, antidepressants, and physical therapy methods or ways, which may affect the depression symptoms during the treatment period. All participants have to provide written, informed consent.

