**FIGURE 2 F2:**
[figure not shown]
Illustration of Transcutaneous electrical cranial-auricular acupoint stimulation (TECAS).

For patients who will receive escitalopram treatment, oral administration escitalopram tablets will be prescribed by clinical psychiatrists with respect to patients’ conditions for 8 consecutive weeks. The usual dosage is 5 mg daily in the first week and 10 mg daily from the second week. Clinicians can increase the maximum daily dose to 20 mg daily depending on the patient’s response, condition, and course of the disease. For elderly patients (>65 years of age), it is recommended to start the treatment at half of the usual starting dose described above, and the maximum dose should be reduced accordingly.

In terms of the drug combination, for patients with severe insomnia, the treatment group and control group can be combined with weak diazepam or non-benzodiazepine sedative drugs; the drug use should be recorded in the case report form (CRF). The MADRS score, the 17-item Hamilton Depression Rating Scale (HAMD-17) score, the Hamilton Anxiety Rating Scale (HAMA) score, the Pittsburgh Sleep Quality Index (PSQI) score and the Short Form 36 Health Survey (SF-36) will be assessed by trained research assistants at baseline, 2, 4, 8, and 12 weeks. Adverse events (AE) of all participants will be assessed and evaluated during the whole procedure, as well as laboratory tests (blood routine, urine routine, and electrocardiogram) if needed.

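### The primary non-inferiority conclusion rests on the per-protocol set alone, with no stated analysis of all randomised patients to support it

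*Protocol article*

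**What the plan says.** All references are to the protocol article.

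- **Statistical Analysis, population:** "The primary outcome will be evaluated based on the per-protocol (PP) population, defined as all randomized populations without major protocol violations". No intention-to-treat, full-analysis or all-randomised analysis of the primary outcome is stated anywhere.
- **Statistical Analysis, missing data:** "Missing data for the primary outcome will be imputed using the multiple imputation method under the missing at random assumption". As the robustness check, "a sensitivity analysis will be performed without multiple imputation". No second population is named for it.
- **Participants:** "Participants were prohibited to use any other drug or non-pharmacological therapy, including phytomedicine, antidepressants, and physical therapy methods or ways", where these may affect depressive symptoms during treatment. The ban applies to both arms.
- **Intervention Procedure, escitalopram arm:** "Clinicians can increase the maximum daily dose to 20 mg daily depending on" response, among other things.
- **Randomization:** "Participants, clinical psychiatrists, and treatment technicians will be aware of the treatment condition". Outcome assessors are described as blinded.

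The article does not define which protocol violations are major.

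**The concern.** A per-protocol analysis is a recognised part of a non-inferiority trial, because analysing everyone as randomised can dilute a real difference. That is a reason to report both analyses, not to let the per-protocol set stand alone. The per-protocol set conditions on what happens after randomisation, so the comparison is no longer protected by the randomisation.

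Here what happens afterwards can plausibly differ by arm in a way tied to outcome. A TECAS patient who is doing badly and starts an antidepressant breaks the ban and may be excluded. An escitalopram patient who is doing badly can have the dose raised and remain within the protocol. The people who decide on added treatment know the allocation. Assessor blinding protects the scoring of the MADRS; it does not affect who is excluded.

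The stated sensitivity analysis cannot reveal this. Dropping the imputation leaves the population unchanged, and imputing missing scores does not bring back patients who have been excluded. What is at stake is a false claim that TECAS is non-inferior, which is the trial's main conclusion.

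**Working it through.** **Inputs from Statistical Analysis and Randomization.** Total 470, allocated 1:1; 20% loss to follow-up; margin −10 percentage points; pilot response rates 83.3% (TECAS) and 80.0% (escitalopram); primary test at one-sided 0.025.

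**The plan's own figure.** The sample size is stated for 90% power at one-sided 5%. With the unpooled normal formula, n per arm = (z₁₋α + z₀.₉₀)² × (0.80×0.20 + 0.833×0.167) / 0.133².
- At 0.05: 145 per arm, 290 in total, 290/0.8 = 363 after allowing for dropout.
- At 0.025: 178 per arm, 356 in total, 356/0.8 = 445. The Farrington–Manning version gives 455 and a continuity-corrected version 483.

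So 470 fits the 0.025 test level and not the 5% stated with it. That is a separate matter and does not affect this point. The number evaluable is 470 × 0.8 / 2 = 188 per arm.

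**Assumptions.** True response is 70% on TECAS and 80% on escitalopram, exactly at the margin, so a valid test declares non-inferiority 2.5% of the time. Shares xT and xE of the 188 patients in each arm are excluded, and all of those excluded are non-responders. The article gives no exclusion share, so a range is shown.

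**Formulas.** The per-protocol rates are pT = 0.70/(1 − xT) and pE = 0.80/(1 − xE), with nT = 188(1 − xT) and nE = 188(1 − xE). Let D = pT − pE and SE = √[pT(1 − pT)/nT + pE(1 − pE)/nE]. The chance of declaring non-inferiority is Φ[(D + 0.10)/SE − 1.96].

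**Worked case, 5% on TECAS and 0% on escitalopram.** pT = 0.70/0.95 = 0.7368; D = −0.0632; nT = 178.6; SE = 0.0440; (−0.0632 + 0.10)/0.0440 = 0.837; Φ(0.837 − 1.96) = 13.1%.

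| Failures excluded, TECAS / escitalopram | Per-protocol difference (points) | False non-inferiority |
|---|---|---|
| 0% / 0% | −10.0 | 2.5% |
| 2% / 0% | −8.6 | 5.1% |
| 5% / 0% | −6.3 | 13.1% |
| 10% / 0% | −2.2 | 43.5% |
| 5% / 2% | −8.0 | 6.8% |
| 10% / 5% | −6.4 | 13.3% |
| 5% / 5% | −10.5 | 1.9% |
| 5% / 10% | −15.2 | 0.06% |

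An imbalance is enough to inflate the error; exclusions need not be confined to TECAS. Equal exclusion slightly widens the difference (−0.10/0.95 = −0.105), and heavier exclusion on escitalopram works strongly against non-inferiority.

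**Can the trial afford an all-randomised analysis?** At the pilot rates and one-sided 0.025, power is Φ(0.133/SE − 1.96). With 235 per arm, SE = 0.0357 and power is 96.1%. With 188 per arm, SE = 0.0399 and power is 91.5%. Imputed outcomes add less information than observed ones, so the value in practice should lie between the two if the pilot rates hold.

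**The case against.** The strongest objection is that the direction of bias is not established, and that stands. A reader might infer that TECAS failures who start an antidepressant are certain to be excluded, so that the analysis must favour TECAS. The article does not support that. It does not define a major violation, and detailed per-protocol criteria are commonly left to a fuller document. The ban covers both arms, so an escitalopram patient who adds or switches treatment breaks it too. The Introduction itself stresses poor adherence to antidepressants, which could lead to exclusions in that arm. The last two rows of the table show the bias disappearing or reversing.

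A reader might also take the permission for sedatives in severe insomnia as a contradiction that makes per-protocol membership unclear. It reads more naturally as a specific exception to a general ban, and it applies equally to both arms, so it adds nothing to an argument about imbalance. Nor does the article say that unblinded staff decide membership. How that is decided and locked is ordinary content for an analysis plan that is not shown.

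Finally, analysing everyone as randomised is not automatically safer. If TECAS failures improve on an added antidepressant, their observed week-8 scores would also favour non-inferiority. That stands, and it is why the fix needs a rule for such patients.

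None of this removes the core point. The per-protocol set is a stated choice, not a detail left open, and it is the only population stated for the primary test.

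**Conclusion.** The point holds. The plan as published bases its main conclusion on a population selected after randomisation and states no randomised comparison beside it. The features described in the article make heavier exclusion of failures on TECAS plausible, and that is the direction that produces a false claim. They do not show that it will happen.

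Under the assumptions above, heavier exclusion on TECAS raises the false-positive rate from 2.5% to between 5.1% (2%/0%) and 43.5% (10%/0%), with 6.8% and 13.3% when both arms lose some failures (5%/2% and 10%/5%). Balanced exclusion or heavier exclusion on escitalopram takes it below 2.5%. These figures rest on assumed exclusion shares, on every excluded patient being a non-responder, and on true rates lying at the margin. They show how sensitive the conclusion is and do not forecast the trial's error rate. The lack of a stated all-randomised analysis does not depend on them.

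**What to change.** State in the protocol and analysis plan that non-inferiority is concluded only if the lower limit of the two-sided 95% interval for the difference in response (TECAS minus escitalopram) lies above −10 percentage points in both of these sets:

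1. All randomised patients, analysed as randomised, with the start of a prohibited antidepressant treatment before week 8 counted as non-response. This is a rule for the analysis only and leaves patient care unchanged.
2. The per-protocol set as now planned.

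The cost is a change of wording and one more run of the same analysis. Requiring both sets to pass slightly lowers the chance of a positive result. On the pilot rates no larger sample is needed, since 235 per arm gives about 96% power at one-sided 0.025. That figure assumes that the pilot rates hold in the all-randomised set; counting patients who start prohibited treatment as non-responders could lower the observed rate in either arm.

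### The only test named for the primary response rate, a site-stratified Cochran-Mantel-Haenszel test, has a null of no difference and does not use the −10% non-inferiority margin

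*Protocol article*

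**What the plan says.** The abstract of the protocol article describes a non-inferiority trial with clinical response on the MADRS as the primary outcome, "at week 8, with −10% as the non-inferior margin". The Statistical Analysis section repeats the margin in its sample-size sentence, which asks for 470 participants and 90% power "at a 1-sided significance level of 5%, assuming a 20% loss to follow-up rate". The pilot response proportion given there "was 83.3% in the TECAS group and was 80.0% in the escitalopram group in our pilot study".

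For the analysis, the same section fixes the level: "The primary outcome will be assessed using a 1-tailed test at a significance level of 0.025". It then names one method for the primary proportion: "the Cochran-Mantel-Haenszel test, stratified by site, will be used to test a hierarchical comparison between two groups". Missing primary outcomes are to be multiply imputed, and the primary population is per-protocol. The margin does not reappear after the sample-size sentence.

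**The concern.** A non-inferiority trial has to reject the null that TECAS is worse than escitalopram by 10 percentage points or more. The standard CMH test has a different null: within each site, response is unrelated to treatment (common odds ratio 1, difference 0). No term in the statistic carries a −10 point shift. The hypothesis the trial is sized on and the test named for it are therefore not the same.

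The trial's single confirmatory conclusion rests on this sentence. An analysis that followed it would demand superiority from a trial sized to show non-inferiority. An analysis that departed from it would contradict the published protocol, possibly after results were known.

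**Working it through.** **Inputs, all from the protocol article.** Response 0.833 (TECAS) and 0.80 (escitalopram); margin 0.10; power 90%; one-sided level 0.05 in the sample-size sentence and 0.025 in the analysis sentence; 470 randomised 1:1; 20% loss; five sites. Evaluable patients are 470 × 0.8 = 376, or 188 per arm. If imputation recovered all information on those lost, the figure would be 235 per arm. The two values bracket the answer. Assumed here: near-equal site sizes, the same response rates at every site, and no further loss from per-protocol exclusions.

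**1. The plan's own figure.** For a margin-based comparison,

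n per arm = (z₁₋α + z₀.₉₀)² × [p_T(1−p_T) + p_C(1−p_C)] / (p_T − p_C + 0.10)²

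The variance term is 0.833 × 0.167 + 0.80 × 0.20 = 0.2991. The denominator is 0.133² = 0.01769.

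- One-sided 0.05: 8.564 × 0.2991 / 0.01769 = 144.8, so 145. Then 145/0.8 gives 182 per arm, 364 in total (370 with the Farrington-Manning variance).
- One-sided 0.025: 10.507 × 0.2991 / 0.01769 = 177.7, so 178. Then 178/0.8 gives 223 per arm, 446 in total (456 with Farrington-Manning).

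Neither reproduces 470 exactly. It lies within about 3% of the Farrington-Manning total at 0.025, so the trial's size fits a margin-based test at that level. The conflict between 5% and 0.025 is a separate matter; nothing below depends on it.

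**2. Power at the planning rates, one-sided 0.025.** The standard error of the difference is √(0.2991/n): 0.0399 at 188 per arm and 0.0357 at 235.

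- Null of no difference (CMH): Φ(0.033/0.0399 − 1.96) = Φ(−1.13) = 0.13 at 188; Φ(0.033/0.0357 − 1.96) = Φ(−1.04) = 0.15 at 235.
- Null at the margin: Φ(0.133/0.0399 − 1.96) = Φ(1.37) = 0.915 at 188; Φ(0.133/0.0357 − 1.96) = Φ(1.77) = 0.96 at 235.

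Simulation with five strata and 188 per arm agrees. CMH rejects in favour of TECAS in 12.8% of trials, and the lower 95% limit of the stratified risk difference clears −10% in about 91–92%.

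**3. Both arms at 80%, 188 per arm.** TECAS is then truly non-inferior. CMH rejects in about 2.5% of trials, its nominal level. The margin-based test succeeds in about 68%.

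**4. What a non-significant CMH result would mean.** Take TECAS truly at the margin, 70% against 80%, and a two-sided 5% CMH test.

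- 188 per arm: the null standard error is √(2 × 0.75 × 0.25/188) = 0.0447, so the critical difference is 1.96 × 0.0447 = 0.0875. The actual standard error is √((0.21 + 0.16)/188) = 0.0444. The chance of non-significance is 1 − Φ((0.10 − 0.0875)/0.0444) = 1 − Φ(0.28) = 0.39.
- 235 per arm: 1 − Φ((0.10 − 0.0783)/0.0397) = 1 − Φ(0.55) = 0.29.

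The margin-based test declares non-inferiority here in about 2.5% of trials (2.3–2.8% across simulations). A non-significant CMH result is thus common even when TECAS sits exactly at the margin, and carries no information on whether the margin has been met.

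**The case against.** The strongest reply is that the sentence should be read with its paragraph. Margin, direction and a one-sided 0.025 level are all stated, and together they amount to comparing a lower two-sided 95% limit with −10%. On that reading CMH is shorthand for stratifying by site, and the interval method, variance estimator and decision sentence are details an article may leave to its analysis plan.

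Much of this stands. The intent is clear, and the absence of those details is not held against the article. What remains is that the article does not stay silent on the method: it names one, and that one tests a different null. The word the article uses to describe the comparison could refer to site strata or to non-inferiority followed by superiority. The article does not define it, so it does not resolve the mismatch.

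A reader might infer two stronger claims, and the document supports neither. The first is that the analysis cannot answer the trial's question at all. A significant CMH result favouring TECAS would imply non-inferiority, so it can, but only by way of superiority. That route is not always weak: at 90% against 80%, CMH would reject in about 78% of trials with 188 per arm. The second is that the investigators will treat a non-significant CMH result as proof of non-inferiority. The article nowhere says so. The 29–39% shows why such a result is uninformative; it is not the error rate of a procedure the plan states.

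**Conclusion.** The point holds as a mismatch between the named primary test and the hypothesis the trial is sized on. It is wrong as written, rather than a detail left to the analysis plan. Taken as named, the test has about 13–15% power at 83.3% against 80.0% (188 to 235 per arm), against the stated 90%. A margin-based test on the same data has about 91.5–96%. These figures rest on the pilot rates, near-equal sites, common rates across sites and no further per-protocol losses. The mismatch of nulls itself depends on none of them. Since the margin and level are already stated, the remedy is to bring the method into line with them; the design does not need to be rethought.

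**What to change.** Replace the CMH sentence along these lines: *The difference in week-8 MADRS response (TECAS minus escitalopram) will be estimated as the site-stratified Mantel-Haenszel risk difference with Sato variance. The point estimate and variance will be pooled over the imputations by Rubin's rules and a two-sided 95% CI calculated. Non-inferiority will be declared if the lower limit is above −10%.*

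An estimator with a variance is chosen deliberately. A stratified Miettinen-Nurminen interval is a score interval obtained by inverting a test, so Rubin's rules do not apply to it directly; using it would need a stated adaptation.

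The CMH test may be kept as a superiority test carried out only after non-inferiority has been shown, with that order stated.

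The cost is a few sentences and a little analysis programming, with no extra patients or data. The change should be made before allocation is unblinded for analysis.
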